### Statistical analysis and development of the score

4.1

All statistical analyses will be conducted using R packages. Initially, a univariate analysis will be performed to examine the relationship between each pre- and intraoperative variable in the database and the primary outcomes. Variables with *p* ≤ 0.20 and ≤10% missing data will be considered for inclusion in a multivariable model, to ensure sensitivity and prevent the exclusion of potentially relevant factors. Among collinear variables, selection will be based on *p* values and their potential use in constructing an outcome score.

In the multivariable analysis, intraoperative variables will be entered independently and in combination with preoperative variables into a logistic regression model. Both forward and backward stepwise selection procedures will be employed (with entry criteria *p* ≤ 0.10 and inclusion criteria *p* ≤ 0.05) for outcomes of interest. The final model will be selected based on the Akaike Information Criterion (AIC). Variables that independently predict major complications or death will be considered as candidates for the risk index score. Alternative combinations of variables for the risk index score will be compared, emphasising simplicity, clinical safety, and predictive power.

After determining the final variables for inclusion, the magnitude of the β coefficients from the regression equation will be used to assign weights to each variable. Depending on the number of variables included, the score will be represented as either a 10-point or a 20-point scale. The intervals and cut-offs for each point level will be designed to ensure that a 1-point increase in the score corresponds to a proportional increase in the odds of a complication. The values for each cut-off will then be rounded to clinically relevant figures that can be recalled easily by surgeons. For instance, operation duration will be valued as follows: 0 points for ≤120 min, 1 point for 120–180 min, etc.

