Logistic regression will be used to examine the relationship between major complications/death, and the risk index score (treated as an ordered categorical variable based on predefined categories) and its components across the three patient cohorts. Model discrimination will be assessed by calculating c-statistics (area under the receiver operating characteristic curve). For model calibration, the Hosmer-Lemeshow (HL) goodness-of-fit test will be used to compare predicted versus observed outcomes between the two cystectomy cohorts. In the final cohort, differences in complication rates across individual scores will be compared using chi-square tests. Additionally, using morbidity (complicated/uncomplicated) and mortality (dead/alive) as dichotomous dependent variables, multiple logistic regression models will be derived. Overall model significance will be assessed via the model chi-square statistic, and differences between observed and expected outcomes will be evaluated using the HL test.

To develop the surgical difficulty index, pre-, intra-, and postoperative parameters and outcome measures will be determined by experienced high-volume surgeons (≥1000 major interventions and >10 yr of surgical experience) using the Delphi method. Pre- and perioperative parameters that potentially increase operative difficulty and risk will be assessed using a 5-point scale, as shown in Supplementary Tables 1–3. Primary outcome measures for surgical difficulty will include operation duration, blood loss and transfusion, use of haemostatic agents, and the surgeon’s judgement (on a scale from 0 to 100).

The performance of the universal surgical risk calculator, which includes multiple specialities and hundreds of procedures, will be compared with the performance of our risk calculators, specifically programmed for this score development. This comparison will be made for individual procedures (eg, RC and RP).

Alternatively, to create risk prediction models, random-intercept, fixed-slope hierarchical models (using SAS GLIMMIX) will be employed. These models account for case clustering within hospitals and impose an empirical Bayes-type shrinkage adjustment. As a result, both universal and procedure-specific surgical risk calculators will be developed. The performance of the universal versus procedure-specific models will be evaluated using three metrics: the c-statistic, the HL statistic (in a revised graphical form), and the Brier score.

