Prediction models for mortality, CCI, blood loss, operating time, and other outcomes will be developed using logistic regression with stepwise selection based on the AIC. Cumulative C-indices will be recorded at each step of model development.

Given the HL test’s sensitivity to sample size, graphs will be constructed based on sequential groups with equal observed events rather than equal patient numbers (thus, low-risk groups will have more patients than high-risk groups).

For evaluating risk prediction accuracy and comparing the universal and procedure-specific surgical risk calculators, the Brier score will be considered the most appropriate measure of model performance. Results from 2 yr of data used for model development will be compared with those from the 3rd year of data used for validation.

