### Internal validation

4.3

Internal validation of the prediction models will be conducted by randomly splitting the analytic dataset into two subsets: a developmental dataset (two-thirds of the total data) and a validation dataset (one-third of the total data). The C-indices, HL analyses, and Brier scores from the logistic regression analyses will be compared between the developmental model applied to the developmental dataset and the same model applied to the validation dataset.

The use of stepwise, forward-selection logistic regression has faced criticism, particularly in small samples, regarding variable selection and the accuracy of the coefficients and standard errors. However, such criticisms are less relevant when applied to the large sample sizes present in this study. To further test the robustness of the model, bootstrap resampling will be employed for the postoperative mortality model. Full-variable logistic regression models will be performed on each bootstrap sample. The variables will then be ranked by the magnitude of the Wald χ^2^ statistic, and the average rankings from the bootstrap samples will be compared with the order of entry of variables during the forward selection stepwise regression analysis. As such, all steps described above aim to minimise overfitting and improve predictive accuracy.

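### The model chi-square p value for the morbidity and mortality models is not valid, because the model terms are selected on the same outcome data

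*Protocol article*

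**What the plan says.** Section 4.1 of the protocol article starts from "each pre- and intraoperative variable in the database" and relates each one to the primary outcomes. It then applies a screen: "Variables with *p* ≤ 0.20 and ≤10% missing data will be considered for inclusion in a multivariable model". Next comes selection, described in these terms: "Both forward and backward stepwise selection procedures will be employed (with entry criteria *p* ≤ 0.10 and inclusion criteria *p* ≤ 0.05) for outcomes of" […]. AIC decides which model is final. For mortality and several other outcomes the section says again that models "will be developed using logistic regression with stepwise selection based on the AIC".

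The same section says that, "using morbidity (complicated/uncomplicated) and mortality (dead/alive) as dichotomous dependent variables, multiple logistic regression models will be derived". The next sentence gives the test at issue: "Overall model significance will be assessed via the model chi-square statistic, and differences between observed and expected outcomes will be evaluated using the HL test". It mentions no allowance for selection and does not say that the test is run on held-out data.

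Section 4.3 splits the data at random into a development two-thirds and a validation third. The measures compared across the split are listed: "The C-indices, HL analyses, and Brier scores from the logistic regression analyses will be compared between the developmental model applied to the developmental dataset" on one side, with its application to the validation third on the other. The model chi-square is not among them. Section 4.3 also argues that objections to stepwise selection matter less in a sample of this size.

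**The concern.** The model chi-square asks whether the fitted model has any relation to the outcome. It compares the likelihood-ratio statistic with a chi-square distribution whose degrees of freedom equal the number of terms in the model. That comparison is correct only if the terms were fixed before the outcome was looked at. Here the terms are the ones, out of a larger pool, that looked best against the same outcome. The statistic is the maximum of a search but is judged as if no search had taken place.

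At stake is the meaning of one reported result. A reader who sees that the morbidity or mortality model is significant overall will take this as evidence of real signal. If the test would say so most of the time for noise, it is close to no evidence.

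**Working it through.** The article states no error rate for this test, so there is no figure of its own to reproduce. The check is the rejection rate under a global null, in which no candidate predicts the outcome.

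**Inputs**
- Number of predictors: 10 to 30 (section 3.7).
- A larger pool is possible, because section 4.1 screens all database variables without giving a count. Table 2 lists 14 + 13 + 2 general and 12 + 13 prostatectomy-specific entries, 54 in all, or 53 distinct because BMI appears twice.
- Selection: screen at p ≤ 0.20, entry 0.10, retention 0.05, or AIC (section 4.1). For a single 1-df term, AIC keeps it if its chi-square exceeds 2, that is p < 0.157.
- Test level: 5%, assumed. Section 3.7 gives 0.05 for the sample size, and no level is stated for this test.
- Event rates: assumed, 5% to 30%.

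**Closed form for the p-value rule**

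With independent candidates, every retained term contributes at least 3.84 to the model chi-square. For 1, 2 or 3 retained terms the sum is at least 3.84, 7.68 or 11.52, against 5% critical values of 3.84, 5.99 and 7.81. So once any term is retained, the overall test is significant. The false rejection rate is the chance that at least one of k null candidates reaches p ≤ 0.05:

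1 − 0.95^k
- k = 10: 1 − 0.599 = 0.40
- k = 30: 1 − 0.215 = 0.79
- k = 54: 1 − 0.063 = 0.94

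**Simulation, independent candidates, nominal 5%**

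| Candidates | p ≤ 0.05 retention, large-sample limit | AIC, large-sample limit | Same model, no selection |
|---|---|---|---|
| 10 | 39.5% | 46.7% | 4.8% |
| 20 | 64.2% | 77.5% | 5.0% |
| 30 | 78.4% | 91.6% | 4.9% |
| 54 | 93.9% | 99.5% | 5.1% |

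Finite-sample logistic regressions agree:
- n = 787 (two-thirds of 1180), 300 runs per setting, event rates 20% and 5%: the p-value rule gives 37–38% with 10 candidates and 79–82% with 30. AIC gives 45–54% and 92%.
- n = 1000 with 30% events and n = 1550 with 5% events: across rules, 40–51% with 10 candidates and 79–93% with 30.

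**Correlated candidates** (pairwise correlation 0.3 to 0.5, large-sample limit): about 32–47% with 10 candidates, 64–92% with 30, and 82–99.6% with 54. The lower ends fall and the upper ends barely move.

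**Does sample size help?** No. The table above is the large-sample limit, and the inflation is still there. The argument in section 4.3 does not cover this test.

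**After the fix.** Testing the frozen linear predictor on independent data rejected in 3.3–5.2% of runs in the large-sample limit and in 2–7% of the finite-sample runs.

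**Power of the held-out test** (validation n = 1180/3 = 393, assumed c-statistic 0.65, Hanley-McNeil standard error):
- 20% events (79 events, 314 non-events): SE 0.036; 0.15/0.036 ≈ 4.1; power about 98%.
- 5% events (20 events, 373 non-events): SE 0.068; 0.15/0.068 ≈ 2.2; power about 60%.

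**The case against.** The strongest reply is that nothing depends on this test. The score is built from multivariable selection, AIC and judgements of simplicity, clinical safety and predictive power. Section 4.1 names the Brier score as the preferred measure of accuracy, and section 4.3 carries the C-index, Hosmer-Lemeshow analysis and Brier score to held-out data. A pure-noise model would show a C-index near 0.5 there. Such a model is also unlikely, since section 3.7 says factors were chosen partly for predictive value and the candidates include age, ASA class, blood loss and operating time.

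Most of this stands, and it limits the point. Several stronger conclusions are tempting, but the article does not support them:
- **That a noise model could reach the calculator on the strength of this p value.** No section makes the chi-square a condition for that.
- **That the procedure-specific models are affected.** Section 4.1 evaluates the universal and procedure-specific models by c-statistic, Hosmer-Lemeshow and Brier score, and attaches the model chi-square only to the morbidity and mortality models.
- **That false significance is near-certain at 99%.** That needs about 50 or more screened variables, and Table 2 is a proposed list drawn up before the Delphi rounds. At 30 candidates the maximum is about 93%.
- **That the inflation is worst for rare events.** The simulated rates at 5% and 20% events are nearly the same.

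Two links are also inferred. Selection is explicit for mortality, but for morbidity it follows from the general selection paragraph in section 4.1. The 5% level comes from the sample-size paragraph.

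What the reply does not remove is that the article fixes a test whose p value is wrong for the models it is applied to. Checks by other measures do not make that p value valid.

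**Conclusion.** The point holds as a fault in one stated analysis. The in-sample model chi-square of a selected morbidity or mortality model has no valid p value. Under a global null with independent candidates and an assumed 5% cut-off, it rejects in about 40–50% of cases with 10 candidates and 80–93% with 30. It would reach 94–99% only if about 50 or more variables were screened. Correlation among candidates lowers the bottom of each range, to about 32% with 10 and 64% with 30.

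The practical weight is modest. What is lost is the information in one significance statement; the planned held-out measures still protect against mistaking noise for a useful model. The conclusion rests on reading section 4.1's selection steps as applying to both outcomes. A fully prespecified model with no selection would keep the test at about 5%.

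**What to change.** In section 4.1, replace the statement on overall model significance along these lines:

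> For the selected morbidity and mortality models, the in-sample model chi-square will be given descriptively, without a p value. Where a significance statement is made, the coefficients of the model selected in the development two-thirds will be frozen, and its linear predictor tested by a 1-df likelihood-ratio test in the validation third. For mortality, a permutation test will be used: the outcome is permuted, the whole screen and selection are rerun each time, and the observed model chi-square is compared with the resulting distribution.

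If outcomes are permuted within centre, small centres should be pooled where a stratum would otherwise contain no events. This matters because the source database spans 178 centres.

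The cost is a change of wording, a little extra code and some computing time for the permutations. No new data are needed, because the split is already planned in section 4.3. The drawback is reduced power in the validation third. Under the assumptions above (c-statistic 0.65, n = 393) it is about 98% at a 20% event rate but only about 60% at 5%, which is why the permutation test is suggested for mortality. If no significance statement is needed, the descriptive report alone is enough.

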2	To predict intra-, peri-, and postoperative outcomes by considering preoperative factors only, to optimise the allocation of critical care resources or defining teaching-appropriate cases before surgery starts
3	To determine surgical difficulty as a separate matter to judge surgical performance by improving the comparison of intra- and postoperative outcomes between surgeons and between different interventions
4	To define parameters that make certain operations (and approaches) for anaesthetists and urologists more difficult
5	To create several indices (surgical risk and difficulty estimation) that are calculated before and immediately after surgery

The surgical difficulty and risk estimation tool will integrate five categories of patient-specific parameters (Table 2):1.Preoperative (known, expected) patient-specific characteristics and conditions (eg, body mass index [BMI], ASA score, sex, prior abdominal surgery, and comorbidities)2.Intraoperative (unknown or unexpected) body/patient-specific characteristics and conditions (eg, bleeding tendency, restricted operative space due to a narrow bony pelvis, or extensive adhesions)3.Preoperative targeted organ-specific parameters (eg, tumour size and location, organ anatomy and morphology, or a history of prior interventions on the targeted organ such as biopsies or transurethral resection of the prostate preceding prostatectomy)4.Intraoperative targeted organ-specific parameters (eg, fibrosed periprostatic tissue or tumour extension beyond the targeted organ).5.Unexpected/unknown postoperative conditions prior to discharge or within 24 h (eg, acute kidney injury, quantified by a decrease in glomerular filtration rate [ml/min])

Surgical and anaesthetic parameters will be evaluated independently to account for the influence of case volume and individual learning curves on surgical complexity and risk. The key variables will include the total case volume, frequency of procedures performed within a defined period, and complexity of prior cases. Additionally, institutional case load will be considered when estimating perioperative morbidity risk (eg, in tertiary referral centres).

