### Identification and description of factors

3.3

In the initial phase of the study, risk-predicting parameters will be defined using data from the CAMUS Collaboration cystectomy database, which will include pre- and intraoperative variables sourced from 178 centres worldwide. Additional parameters from a prospective open cystectomy database maintained by the Urology Department at the University of Bern will further enhance data collection. The difficulty estimation score will be developed and validated using these data, supplemented by prospectively collected parameters detailed in round 1 of the study.

The RC cohort will be selected as the primary focus due to its high complication rate and clinical relevance. In subsequent phases, the scoring system’s performance will be assessed in various patient cohorts who have undergone RP, PN, radical nephrectomy (RN), radical nephroureterectomy (RNU), and retroperitoneal lymph node dissection (RPLND).

The first Delphi round will involve expert consensus to identify parameters influencing peri- and postoperative morbidity, mortality, and surgical difficulty. For example, parameters relevant to RP will be outlined in Supplementary Tables 1 and 2. Experts will be guided by the results derived from nomograms. Organ-specific factors, as part of the organ-specific scoring system, will also be examined for procedures such as RC, RP, PN, RN, RNU, and RPLND, with further details provided in Supplementary Table 3.

To assess the impact of these parameters on both difficulty and risk, a comprehensive description of the associated conditions and characteristics will be required. These parameters will be categorised according to a five-level scale of difficulty: easiest, intermediate easy, standard, intermediate difficult, and most difficult. For instance, preoperative BMI ranges will be classified as follows: BMI 18–22 kg/m^2^ will correspond to the easiest grade, while BMI >40 kg/m^2^ will be categorised as most difficult. Similarly, for organ-specific factors such as prostate size in RP, a prostate volume of 20–30 cc on magnetic resonance imaging will represent the easiest level of difficulty, whereas a volume exceeding 200 cc will be classified as most difficult.

Notably, multiple conditions may be associated with the same level of difficulty. For example, multiple prior open procedures or laparoscopic surgeries involving mesh insertion may be considered of intermediate difficulty.

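### Section 4.1 states variable-selection rules that conflict and, separately, does not settle whether the single-level or the hospital random-intercept model supplies the score weights

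*Protocol article*

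**What the plan says.** **Selection.** The opening paragraphs of section 4.1 (Statistical analysis and development of the score) start with a univariable screen: "Variables with *p* ≤ 0.20 and ≤10% missing data will be considered for inclusion in a multivariable model". The survivors go into a logistic regression, where "Both forward and backward stepwise selection procedures will be employed" ("with entry criteria *p* ≤ 0.10 and inclusion criteria *p* ≤ 0.05"). The final model is then chosen by AIC, and the size of its β coefficients sets the points in the score. The target is major complications or death. Towards the end of the same section, models for mortality, CCI, blood loss, operating time and other outcomes are to be "developed using logistic regression with stepwise selection based on the AIC", with no p-value thresholds. Section 4.3 (Internal validation) refers to forward selection only.

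**Clustering.** Section 3.3 describes the CAMUS cystectomy database, "which will include pre- and intraoperative variables sourced from 178 centres worldwide". The regression that selects and weights variables in section 4.1 has no stated centre or surgeon term. Several paragraphs later the section adds: "Alternatively, to create risk prediction models, random-intercept, fixed-slope hierarchical models (using SAS GLIMMIX) will be employed". It says these models account for clustering within hospitals and shrink estimates, and that the universal and procedure-specific calculators result from them. It does not say which of the two models supplies the score weights.

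**Centre- and surgeon-level factors.** Section 2.2 says "institutional case load will be considered when estimating perioperative morbidity risk". Section 3.6 divides surgeon experience into six case-volume stages.

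**The concern.** A score built from regression coefficients is fixed by two decisions: which variables are kept, and which model estimates their weights. Section 4.1 answers each in more than one way.

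On the first, two analysts following different sentences of the section could publish different scores from the same data. The quoted stepwise thresholds are also in an unusual order, because entry is easier than staying in.

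On the second, patients treated in one hospital tend to have correlated outcomes. A single-level model ignores this, and its standard errors are then too small for covariates that do not vary within a hospital or surgeon. The protocol means to take caseload and experience into account, so this type of covariate matters here. The two defects are independent: repairing one leaves the other in place.

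**Working it through.** The plan gives no figure of its own on either point to reproduce. Its required sample size of 1180 is not disputed here.

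**Part 1: the rules side by side**

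Inputs from section 4.1: screen p ≤ 0.20; entry p ≤ 0.10; inclusion p ≤ 0.05; AIC for the final model; AIC-only stepwise for mortality and other outcomes.

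AIC keeps a k-df term when its likelihood-ratio chi-square exceeds 2k.
- 1 df: P(χ²₁ > 2) = 0.157.
- 5 df (for example a six-stage experience factor, if entered as categories): P(χ²₅ > 10) = 0.075.

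Fate of a 1-df term, by its p value in the multivariable model:

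| p value | Stepwise p rule | AIC rule |
|---|---|---|
| ≤ 0.05 | enters, stays | kept |
| 0.05 to 0.10 | enters, then fails inclusion | kept |
| 0.10 to 0.157 | does not enter | kept |
| > 0.157 | does not enter | dropped |

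The rules therefore disagree over the whole range 0.05 to 0.157. They overlap on the same endpoint, since death is part of the main score's outcome and mortality is named again in the AIC-only sentence.

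**Part 2: effect of ignoring centre**

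Inputs: 178 centres (section 3.3). The ICC, the number of patients per centre (m) and the event rate are not given, so they are assumptions and a range is shown.

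For a covariate constant within centre, with equal cluster sizes:
- Design effect DE = 1 + (m − 1) × ICC.
- True two-sided error at nominal 5% = 2 × [1 − Φ(1.96/√DE)].

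| ICC | m | DE | 1.96/√DE | True error at nominal 5% |
|---|---|---|---|---|
| 0.01 | 7 | 1 + 6 × 0.01 = 1.06 | 1.90 | 0.057 |
| 0.05 | 20 | 1 + 19 × 0.05 = 1.95 | 1.40 | 0.16 |
| 0.10 | 50 | 1 + 49 × 0.10 = 5.90 | 0.81 | 0.42 |

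Over 178 centres these cluster sizes imply 178 × 7 = 1246, 178 × 20 = 3560 and 178 × 50 = 8900 patients. In the middle row, a null centre-level covariate passes the p ≤ 0.20 screen 36% of the time.

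The formula was checked by simulating single-level logistic fits: 178 centres of 20, an assumed 30% event rate, 1000 runs per setting, and a latent-scale ICC.

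| Latent ICC | Null centre-level covariate | Null patient-level covariate |
|---|---|---|
| 0 | 0.053 | 0.057 |
| 0.02 | 0.083 | 0.045 |
| 0.05 | 0.134 | 0.057 |
| 0.10 | 0.221 | 0.050 |

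The inflation is confined to the centre-level covariate. The same formula serves a surgeon-level covariate, with patients per surgeon and the surgeon ICC put in.

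**The case against.** On selection, a looser entry and a stricter retention threshold can be called an ordinary two-threshold rule, and AIC may be meant only to choose between the end models of the forward and backward runs. That reading is possible for the opening paragraphs. It does not fit the later sentence, which makes AIC itself the stepwise criterion, and it leaves the 0.10 entry threshold with little purpose, since a term above 0.05 is removed again.

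On clustering, the hierarchical models are said to be employed, and the two calculators to follow from them, so clustering has not been overlooked. That stands. What is missing is a rule saying which model gives the weights. Section 4.1 also says all analyses use R packages and then names SAS GLIMMIX, which suggests the two routes were never reconciled. Most parameters listed in Table 2 are patient-level and, on the simulation above, barely affected. That stands too. Section 4.3 argues that criticisms of stepwise selection matter less in large samples; this does not answer the clustering point, because the design effect grows with patients per centre.

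A reader might infer that volume and learning-curve effects will enter the score on false significance. The article does not support that. Section 4.1 never names them as candidates, and section 3.6 treats experience as strata and a downward adjustment of the index. A reader might also infer one pooled regression in which a single hospital contributes 1550 patients; section 3.7 presents that database as an additional one, and pooling is not stated.

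**Conclusion.** Both defects hold, as separate points.

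The selection conflict is visible from the text alone: for 1-df terms, the outcome between p = 0.05 and p = 0.157 depends on which stated rule is used, and the variables and weights in the score follow from that.

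The clustering point is a raised risk of false inclusion and of intervals that are too narrow. It applies to covariates constant within centre or surgeon, such as institutional caseload or surgeon volume if they are entered. At nominal 5%, the true error runs from about 6%, which is negligible, to 42%, which is serious. Where the study falls in that range cannot be known from the article, because the ICC and cluster sizes are not given and equal clusters were assumed. Nothing here shows that patient-level predictors are wrongly selected.

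**What to change.** **Selection.** State one rule for all risk outcomes: for example, backward elimination by AIC starting from the Delphi-agreed predictors. Delete the univariable screen and the p-value thresholds, and align section 4.3 with the rule. The cost is a less sparse model with some more noise variables: tested on its own, a null 1-df term survives AIC with probability about 0.157, against 0.05 under the inclusion threshold.

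**Clustering.** Make the hospital random-intercept logistic model, already planned, the primary model for the risk outcomes and the stated source of the weights. Add a surgeon intercept where surgeon identity is recorded, because a hospital intercept alone does not cover surgeon-level experience. Carry out the selection within this model, fitted by a true likelihood method so that AIC is defined, and name one software environment. Keep the single-level model as a sensitivity analysis. The cost is wording, code and somewhat heavier computation, with wider intervals for centre- and surgeon-level effects. No new data collection is needed for the hospital intercept, provided hospital is recorded, as the planned model already requires.
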